### Data collection

Data collection will be conducted at the first visit and at each follow-up interview using standardized, structured questionnaires. The questionnaires have been developed based on questionnaires used in Hong Kong [3,29].

Baseline data will be collected during the first visit via a face-to-face interview. The collected data will include demographic characteristics (gender, age, marital status and educational level); self-reported perceived health status over the past several days (very good, good, fair, poor, very poor); smoking history (smoking status, the age at starting smoking regularly and the average number of cigarettes smoked per day); the six questions regarding nicotine dependence levels based on the Fagerström Test for Nicotine Dependence (FTND) [30]; past quitting history (whether attempts have ever been made to quit, past use of cessation products and causes of relapse); and whether the participant has any doctor diagnosed chronic diseases. Body weight will be measured in kilograms (shoes and heavy clothing will be removed, and one kilogram will be deducted for the participant’s remaining garments), and exhaled carbon monoxide level will be measured using a “Bedfont Micro II Smokerlizer” [3].

Follow-up data will be collected via telephone interviews at 1 week and 1, 3, 6 and 12 months after the first interview; questions will address smoking or smoking-reduction status, quitting attempts and withdrawal symptoms. Participants who report having abstained from smoking for more than 7 days at the 12-month follow-up will be invited to do a face-to-face biochemical verification (i.e., exhaled carbon monoxide level will be measured).

### Randomization

Before participant recruitment, a research assistant on the project will generate random numbers for group assignments using a computer. If an individual is eligible to participate in the study, and written consent is obtained, trained counselors will randomly allocate the participant to a treatment group by opening a serially labeled, opaque and sealed envelope, and a card inside will indicate the group to which the participant should be randomly allocated.

### Blinding

Given the nature of the intervention, it will be impossible to blind the subjects to their group assignments. However, the trained counselors who will conduct the telephone follow-up interviews will be different from the ones who completed the first interview and will not know the aim of the subjects; they will therefore be able to record outcome measures with minimal subjective bias. The researchers who will conduct the data analysis will be blinded to any potential identifiers.

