### Smoking-reduction intervention group (SRI)

In the first face-to-face interview, trained counselors will give each smoker a very brief smoking-reduction intervention lasting approximately one minute. Smokers will be warned that many non-communicable diseases are caused by smoking, such as cancer, coronary heart disease, respiratory diseases and many other health problems. Moreover, one out of two smokers will be killed by smoking [31]. Smokers will be advised to reduce smoking consumption to at least half of their total consumption within the next month. Finally, all smokers will be asked to bear in mind that the current attempt to reduce smoking would be an intermediate step before complete cessation.

The tobacco-use status of each smoker will be assessed by another trained counselor who will not know the aim of the project at 1 week and 1, 3, 6 and 12 months via telephone follow-ups. Additional smoking cessation interventions will be given at each follow-up according to their updated smoking status. Smokers will be encouraged to reduce their smoking consumption if they have not changed their smoking status, and smokers who have successfully reduced their smoking consumption will be encouraged to quit completely; smokers who have successfully quit smoking will be supported to maintain abstinence. Each follow-up will last for about one minute.

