### Exercise- and diet-advice group (EDA, Controls)

In the first face-to-face interview, trained counselors will give each smoker very brief advice for about one minute. Smokers will be advised to engage in regular physical activity three or four times per week and to have a healthy and balanced diet including more fruits and vegetables, which are rich in vitamins, high in nutrition values and yet low in calories.

The tobacco-use status of each smoker will be assessed at each follow-up interview, similar to the SRI group. Smokers will be advised to engage in regular physical activity and to eat more fruits and vegetables. Each follow-up will last approximately one minute. Throughout the process, smoking cessation or smoking reduction will not be mentioned.

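### Follow-up callers most likely know the arm because the same calls deliver arm-specific advice, so the claim of minimal subjective bias is not supported

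*Protocol article*

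**What the plan says.** All references are to the protocol article. The Blinding section accepts that participants cannot be blinded. Its safeguard for outcome recording is that "the trained counselors who will conduct the telephone follow-up interviews will be different from the ones who completed the first interview" and that these counselors do not know the participants' aim, from which it concludes that "they will therefore be able to record outcome measures with minimal subjective bias". The section on the SRI group repeats this: tobacco use is "assessed by another trained counselor who will not know the aim of the project at 1 week and 1, 3, 6 and 12 months".

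The two arm descriptions then say what the follow-up contacts contain. In SRI, "Additional smoking cessation interventions will be given at each follow-up according to their updated smoking status". In EDA, "Smokers will be advised to engage in regular physical activity and to eat more fruits and vegetables", with the restriction that "Throughout the process, smoking cessation or smoking reduction will not be mentioned". Each contact lasts about one minute in both arms.

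The Abstract counts the five follow-ups as interventions. Data collection obtains the outcome data by telephone interview at 1 week and 1, 3, 6 and 12 months. Outcome assessments expects about 10% of smokers to return for the biochemical test and makes self-reported quitting the primary measure if few do.

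**The concern.** The conclusion in the Blinding section rests on two facts: the caller is a new person, and the caller does not know the aim. Neither hides the allocation. Someone who gives quit advice to one participant and only diet advice to the next must be told which applies, and so knows the arm whether or not the trial's hypothesis has been explained.

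The primary outcome may well be an unverified answer given in such a call. A caller who knows the arm can, without intending to, probe less or accept a doubtful answer more readily in one arm. If that happens more in SRI, the error raises the SRI quit rate and looks like benefit. Later analysis cannot separate it from a real effect.

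**Working it through.** **Step 1. Does the caller need to know the arm?** The relevant sections side by side:

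| Feature of the follow-up contact | SRI | EDA | Section |
|---|---|---|---|
| Times | 1 week; 1, 3, 6, 12 months | same | Data collection |
| Smoking status collected | yes | yes, in a similar way | arm descriptions |
| Advice given | reduce, quit or stay abstinent, depending on status | activity and diet | arm descriptions |
| Cessation or reduction advice | at each contact | ruled out | arm descriptions |
| Length | about one minute | about one minute | arm descriptions |
| Separate adviser described | no | no | – |

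In SRI the advice depends on the status just reported, so assessment and advice belong to the same contact. One contact of about one minute, run by the counselors who conduct the follow-up interviews and with no second person mentioned, points to one caller doing both. That caller must know the arm to give the right advice. By the 12-month call a participant may have had four earlier follow-up contacts, so a returning caller could also recall the arm.

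**Step 2. Does this reach the primary outcome?** At the planning rates with all 331 counted (165 and 166), reported quitters number 0.15 × 165 = 24.75 in SRI and 0.05 × 166 = 8.3 in EDA, about 33 in total. If the expected return of about 10% applies to them, about 3 are tested. On the document's own expectation, the primary result is likely to rest on self-report.

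**Step 3. How sensitive is the comparison to differential false reporting?** The plan gives no figure for this, so these are assumed values.

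- True quit rate 5% in both arms, i.e. no effect. The 5% is the control rate in the Sample-size calculation.
- 165 versus 166. All 331 count because Data analysis treats participants who cannot be contacted as non-quitters.
- Recorded rate: 5% + d in SRI and 5% in EDA, where d is the excess of false quit reports in SRI.
- Test: uncorrected two-sided chi-square at 5%, X² = N(ad − bc)² / (product of the four margins), rejecting if X² > 3.84. The binomial probabilities of all rejecting tables are summed exactly.

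| Extra points d | Extra false quits in SRI (d × 165) | Recorded rates | P(significant) |
|---|---|---|---|
| 0 | 0 | 5% v 5% | 4.9% |
| 1 | 1.65 | 6% v 5% | 6.7% |
| 2 | 3.3 | 7% v 5% | 11.8% |
| 3 | 4.95 | 8% v 5% | 19.8% |
| 5 | 8.25 | 10% v 5% | 41.6% |

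Two variations: with 138 per arm, 3 and 5 points give 16.9% and 35.4%. With a continuity correction at 165 versus 166, they give 13.8% and 33.2%.

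The table describes differential false reporting from any source. It does not isolate the part due to the caller's knowledge.

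**The case against.** **The article never says that the callers are blind to allocation.** This is right. It applies blinding to participants (not possible) and to analysts. Of callers it says only that they do not know the aim, which a caller reading from an advice card might not. A reader might infer that the article claims allocation-blind callers and contradicts itself outright, but the text does not go that far. What fails is the step from not knowing the aim to recording with minimal subjective bias.

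**That assessor and adviser are one person is an inference.** The advice is described in the passive voice, and staffing detail may sit in the full protocol or a manual. It remains the natural reading, since no second person appears and the contact is so short. If a separate adviser exists, the assurance depends on that fact and should say so.

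**Partial protections exist.** Structured questionnaires are used, the first interviewer is a different person, EDA is assessed in a similar way, and claimed quitters are invited for biochemical testing. In SRI, tailoring advice to updated status also implies that status is asked before that call's advice. So it would be wrong to infer that there is no protection. But order alone does not help if the caller already knows the arm, and the expected return weakens the testing.

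**The illustration does not measure the caller's contribution.** This stands in full. SRI participants know their advice and have heard it repeatedly. Some would over-report to any caller, and concealing the arm from callers would remove only an unknown share. The figures also assume no false claims in EDA, and the article gives no source for any value of d. Reading 20% or 42% as the false-positive rate caused by unblinded callers is not supported.

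**Conclusion.** The point holds in a limited form. On the natural reading of the article, the caller who records smoking status also gives arm-specific advice and so most likely knows the arm, including at 12 months. The two reasons offered for minimal subjective bias do not conceal the arm, and the statement is stronger than the procedure supports.

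The size of the resulting bias cannot be derived from the document. The illustration shows only that the comparison is sensitive: about five extra false quits in SRI would take the false-positive rate from about 5% to about 20% under the stated assumptions, while one extra point would take it only to about 7%.

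This should be fixed. It does not invalidate the design, no figure in the plan is wrong because of it, and part of the exposure comes from unblinded participants and the self-report fallback, which would remain with perfectly blinded callers.

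**What to change.** 1. In the Blinding section, withdraw the minimal-bias statement and describe participants' self-report as unblinded. If a separate adviser is in fact used, say so.
2. At every call, and above all at 12 months, ask smoking status first with one identical neutral script in both arms, and lock the answers before the arm-coded advice is opened.
3. At 12 months, book the verification visit before any advice is given.
4. Rotate existing callers so that the 12-month caller has not advised that participant before.

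The cost is a reordered call script, arm-coded advice kept closed until status is locked, and a rota: slightly more call administration and no extra staff. It needs to be in place before follow-up calls begin. It limits bias from the caller's recording and prompting. It does not remove over-reporting by SRI participants who know what they were advised, and the report should state that limitation.

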### Sample-size calculation

Because no similar studies have previously been conducted in China mainland, the effect-size estimation is based on results from Hong Kong [14,24]. We assume that the quit rate at the 12-month follow-up of the SRI group would be 15% versus 5% for the control group. To detect a difference of 10%, it is estimated that 138 subjects would be needed for each group given an alpha level of 5% (two-sided) and a statistical power of 80%. A total of 331 participants will be recruited based on a possible loss of 20% of the participants at the 12-month follow-up.

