### Data analysis

Epidata (3.1) will be used to perform double entry of the collected data. We will use SPSS (IBM Corp. Armonk, NY, USA) for Windows (version 19.0) for data analysis. Baseline characteristics will be compared using chi-squared tests, Mann-Whitney tests and t tests. Regression models will be used to compare the outcomes of different interventions. We will adjust for baseline differences by including the variables in the regression models if necessary. Smokers who cannot be contacted during follow-up will be considered non-quitters or non-reducers in an intention-to-treat (ITT) analysis. For sensitivity analysis, subjects lost to follow-up will be excluded for per protocol (PP) sensitivity analyses.

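### The 20% loss allowance was applied as 276 × 1.2 = 331, but keeping 138 per arm followed up needs 276 / 0.8 = 345, and the ITT analysis does not use the allowance this way (minor)

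*Protocol article*

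**What the plan says.** The Sample-size calculation section assumes that "the quit rate at the 12-month follow-up of the SRI group would be 15% versus 5% for the control group". With a two-sided alpha of 5% and 80% power, it concludes that "138 subjects would be needed for each group". It then adds the allowance for loss: "A total of 331 participants will be recruited based on a possible loss of 20% of the participants at the 12-month follow-up".

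The Data analysis section sets out how losses are handled: "Smokers who cannot be contacted during follow-up will be considered non-quitters or non-reducers in an intention-to-treat (ITT) analysis". Participants lost to follow-up are left out only in the per-protocol sensitivity analyses.

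The article does not say whether the 15% and 5% are proportions of everyone randomised or of those reached at 12 months.

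**The concern.** Two things do not fit together.

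- **The inflation.** The loss is expressed as a share of the participants, that is, of those recruited. The recruited total should then be the required number divided by the share retained. The stated total looks like the required number multiplied by one plus the loss, which always falls short.
- **The link to the analysis.** Raising the headcount for loss makes sense when lost participants leave the analysis set. In the ITT analysis they stay in the denominator as non-quitters. There, loss does not reduce the number analysed; it can only lower the observed quit rates. The allowance therefore serves the sensitivity analysis, and the power of the ITT analysis at 331 is not given.

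At stake is whether the stated 138 per group and 80% power describe the trial that 331 participants will produce, and so how a null result would be read.

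**Working it through.** **Inputs** (all from the article): quit rates 15% and 5%; two-sided alpha 5%; power 80%; 138 per group; 20% loss; 331 recruited (Sample-size calculation); losses counted as non-quitters in the ITT analysis (Data analysis). Equal allocation is inferred from the equal group sizes.

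**1. Reproduce 138.** Unpooled normal approximation for two proportions:

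n = (1.96 + 0.8416)² × (0.15 × 0.85 + 0.05 × 0.95) / 0.10² = 137.4, rounded up to 138.

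This matches, so 138 is sound. The pooled formula gives 141.

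**2. Reproduce 331.** The total required is 2 × 138 = 276.

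- 276 × 1.2 = 331.2, which rounds to the stated 331.
- 276 / 0.8 = 345.

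Only the first operation yields 331.

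**3. What 331 delivers at 20% loss.**

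- 331 × 0.8 = 264.8, about 132 per arm, which is 6 fewer than 138.
- Loss that 331 can absorb while leaving 276: 1 − 276/331 = 16.6%.
- Gap to the consistent total: 345 − 331 = 14 participants, about 4%.

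**4. Power among those followed up, 15% vs 5%.**

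| Method | 138 per arm | 132 per arm |
|---|---|---|
| Unpooled (reproduces 138) | 80.2% | 78.4% |
| Pooled | 79.4% | 77.6% |
| Exact, uncorrected chi-squared | 81.6% | 79.7% |

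With 132 and 133 in the two arms, the exact figure is 80.3%.

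**5. Power of the ITT analysis, about 165 per arm.** The answer depends on what the 15% and 5% represent.

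- *They already count losses as smokers.* The comparison is 15% vs 5% on all 331. Power is 86.7% unpooled and 86.1% pooled. No inflation was needed for this analysis; 276 would have sufficed.
- *They are rates among those reached* (assumption: 20% lost in each arm). The ITT rates become 0.15 × 0.8 = 12% and 0.05 × 0.8 = 4%. Power is 77.3% unpooled, 76.6% pooled and about 78% exact. Reaching 80% would take 177 per arm (unpooled) to 180 per arm (pooled), or 354 to 360 in total. Recruiting 345 would give only about 78–79%.

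So 345 restores 138 per arm followed up, but it is not the ITT sample size under either reading.

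**The case against.** The strongest reply is that the slip hardly matters. The gap is 14 participants. Power among those followed up drops by under two points on the formula that gave 138, and an exact calculation still puts it at about 80%. The lower pooled figure of 77.6% owes part of its distance from 80% to the change of formula, since 138 per arm gives only 79.4% on that formula. The set without losses also serves only the per-protocol sensitivity analysis. The 20% is described as a possible loss, and actual loss could be lower. All of this stands, and it is why the point is minor.

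A second reply is that the 12% vs 4% comparison is a supposition. It needs 15% and 5% to be rates among those reached, and the full 20% loss to fall equally on both arms. The article takes the rates from cited studies that are not at hand, and the full protocol may define the denominator. This also stands: that part is a request for clarification and not a demonstrated error.

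A reader might infer more, namely that a trial of 331 does not have 80% power. The article does not support that as a general statement. If the assumed rates already treat losses as smokers, the ITT analysis has about 86–87% power.

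What the replies do not remove is the arithmetic. No rounding makes 331 recruited, 20% lost and 138 per arm remaining true together.

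**Conclusion.** Wrong as written, and minor. The 20% allowance was applied as a multiplication by 1.2, so 331 supports a loss of about 16.6% and not the stated 20%. At 20% loss about 132 per arm are followed up, and power in that set is 78.4% against 80.2% at 138 on the formula that reproduces the article's figure. This conclusion rests only on the article's own numbers and equal allocation.

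The allowance also does not correspond to the ITT analysis. Power there, with about 165 per arm, is about 86–87% or about 77%, according to whether 15% and 5% already include losses as smokers. The lower figure assumes 20% loss in both arms. The documents do not settle which reading applies, so neither an underpowered nor an overpowered ITT analysis can be asserted.

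**What to change.** Rewrite the end of the Sample-size calculation paragraph. No extra recruitment is needed.

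- Keep 331 and state that it allows for about 16.6% loss with 138 per arm followed up, or that at 20% loss it leaves about 132 per arm and about 78% power among those followed up.
- If 345 is mentioned, say that it is the number that keeps 138 per arm followed up at 20% loss, and that it is not an ITT sample size.
- State whether 15% and 5% are proportions of all randomised, with losses as smokers, or of those reached. Give the ITT power for 331 on that basis: about 86–87% in the first case, about 77% in the second with 20% loss in each arm.

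The cost is one paragraph, and a stated power among those followed up that is slightly less favourable than 80%.

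### The 20% loss allowance is applied by multiplying (276 × 1.20 = 331) instead of dividing (276 / 0.80 = 345), so 331 recruits leave about 132 followed up per group, not 138

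*Protocol article*

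**What the plan says.** The Sample-size calculation section of the protocol article gives all the inputs. The assumed effect is stated as: "We assume that the quit rate at the 12-month follow-up of the SRI group would be 15% versus 5% for the control group". The test is specified "given an alpha level of 5% (two-sided") with "a statistical power of 80"%. From these, "it is estimated that 138 subjects would be needed for each group". The recruitment total follows: "A total of 331 participants will be recruited based on a possible loss of 20% of the participants at the 12-month follow-up". No other section gives a different basis for 331.

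The Data analysis section bears on what a loss does. In the intention-to-treat analysis, smokers who cannot be reached count as not having quit or reduced. Leaving them out is planned as a sensitivity analysis, which the article labels per protocol.

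**The concern.** The paragraph gives three figures: 138 needed per group, a 20% loss, and 331 recruited. They cannot all hold. The loss is expressed as a share of the participants, so the number remaining is 80% of those recruited, and 80% of 331 is less than 276. The recruitment figure looks as if 20% of the number needed at the end was added, when the end number should have been divided by the fraction retained.

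What is at stake is the reliability of the sample-size statement. Readers use it to judge how informative a null result would be, and later trials may copy the calculation.

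**Working it through.** **Inputs** (Sample-size calculation, protocol article): p1 = 0.15, p2 = 0.05, difference 0.10, two-sided alpha 0.05, power 80%, 138 per group, 20% loss, 331 recruited. Equal allocation is assumed: no ratio is stated, but a single number is given for both groups.

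**1. Reproduce 138.** The unpooled two-proportion formula is n = (z0.975 + z0.80)² × [p1(1 − p1) + p2(1 − p2)] / d².

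- Variance sum: 0.1275 + 0.0475 = 0.175.
- n = (1.960 + 0.842)² × 0.175 / 0.10² = 137.4, rounded up to 138. This matches the article.
- The pooled formula gives 140.1, rounded up to 141, so the article appears to have used the unpooled form.

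**2. Reproduce 331.** Total needed: 2 × 138 = 276.

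- Multiplying: 276 × 1.20 = 331.2, that is 331. This matches the article.
- Dividing: 276 / (1 − 0.20) = 345. This does not match.
- Difference: 345 − 331 = 14, which is 4.2% of 331. Rounding does not explain it.

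**3. What 331 delivers.**

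- Retained at 20% loss: 331 × 0.80 = 264.8, or 132.4 per group.
- Largest loss that still leaves 276: 1 − 276/331 = 16.6%.

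**4. Power for 15% versus 5% among those followed up.** Unpooled: Φ(d / √(0.175/n) − 1.96). Pooled: Φ((d√n − 1.96 × √(2 × 0.10 × 0.90)) / √0.175).

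| n per group | Unpooled | Pooled |
|---|---|---|
| 138 | 80.2% | 79.4% |
| 132.4 | 78.5% | 77.7% |
| 132 | 78.4% | 77.6% |

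The slip costs about 1.7 points.

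**5. Power of the intention-to-treat analysis.** All 331 stay in the denominator, 331 / 2 = 165.5 per group. The article does not say what the 15% and 5% refer to, so both readings are shown.

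- *Rates already count losses as non-quitters:* 15% versus 5% at 165.5 per group gives 86.8% (unpooled) or 86.2% (pooled). No inflation for loss was needed.
- *Rates apply to those followed up:* with 20% lost in each group, 0.80 × 15% = 12% and 0.80 × 5% = 4%. Power at 165.5 per group is 77.4% (unpooled) or 76.7% (pooled). With 345 recruited (172.5 per group) it would be 78.4% (pooled), still below 80%.

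**The case against.** The strongest objection is that the shortfall does not touch the intention-to-treat analysis. Nobody leaves that denominator, because losses are counted as non-quitters. The 132 per group and 78% therefore describe only the sensitivity analysis. Nor does the choice between 331 and 345 decide whether intention-to-treat power reaches 80%: on one reading of the assumed rates 331 is comfortably above it, and on the other even 345 falls short. This stands, and it limits the consequence that can be claimed.

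A second objection is size. Moving from the unpooled to the pooled formula already shifts power at 138 from 80.2% to 79.4%. The 20% is offered only as a possible loss, and the effect size is borrowed from Hong Kong results. This also stands: the slip is small beside the other uncertainties.

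A third is that adding 20% is a common shortcut. This does not rescue the figure. The article describes the allowance as "based on a possible loss of 20% of the participants at the 12-month follow-up", and by that description 331 is not enough. Nor is this a detail left to a fuller document, since the conflict lies between figures printed in one paragraph.

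A reader might infer from the slip that the trial as a whole is underpowered, or that recruitment must rise to 345. The document supports neither, because it retains losses in the intention-to-treat analysis and does not say which population the 15% and 5% describe.

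**Conclusion.** The inflation step is wrong as written. This rests only on the article's own figures and on reading the loss as a fraction of those recruited, which is what it says. The recruitment total is 14 below what its stated logic requires, and at 20% loss about 132 per group are followed up where 138 are stated as needed.

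The power figure of about 78% holds only for an analysis of participants who are followed up, assuming equal allocation, equal loss in the two groups, and 15% versus 5% among those followed up. For the intention-to-treat analysis, the article supports only a range, from about 77% to about 86–87%, depending on what the assumed rates mean. The error is certain, its practical effect is minor, and it merits a correction of the text rather than a change of design.

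**What to change.** Correct the sample-size paragraph and leave recruitment at 331. Either of these wordings would do:

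- State that 331 allows for a loss of about 16.6%.
- State that at 20% loss about 132 per group are followed up, with about 78% power for 15% versus 5% in the analysis that excludes losses.

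If the second is used, label the 78% as belonging to that sensitivity analysis. Add that the intention-to-treat analysis keeps all 331 with losses counted as non-quitters, with power of about 86–87% if the assumed rates already count losses that way and about 77% if they are rates among those followed up (12% versus 4% after dilution). Saying which was meant would reduce this to one figure. In either case, show the division 276 / 0.80 = 345 so that the multiplication is not reused.

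The cost is one or two sentences and a slightly less favourable stated loss allowance or power. No extra participants and no change to the analysis are needed.
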